### Settings and Sampling

The target population is adults diagnosed with BD who are under treatment. The recruitment will be implemented in collaboration with the mental health services used by the participants. Specifically, both private and public mental health services in Cyprus have been informed about the objectives and procedures of the study through a specific communication process. Through this process, several patients have already been referred to the research team by their psychiatrists/therapeutic team coordinator to participate in Stage 1. As a result, convenience sampling will be combined with snowball sampling, according to study inclusion criteria set in every stage. The study is also posted on social media and groups related to BD (health care service users, health care professionals).

To promote participant retention, an action plan has been developed. Specifically, the principal investigator (AH) will arrange one or two social meetings with the participants of Stage 1 and Stage 3 to achieve some degree of intimacy, emphasize confidentiality, and ensure engagement with the study. The cost of these social meetings is covered by the Nursing Department of Cyprus University of Technology. Regarding the control group of Stage 3, the principal investigator (AH) will also make a phone call once or twice per month to reassure their participation in the study, as follows: “Hello, I am [name] from the MoB project. I’m calling to see how you are, and if you are still interested in participating in the project. The next appointment will be on date X. Is this okay with you, or do you have any other arrangements for the day?”

### Stage 1

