#### Inclusion and Exclusion Criteria

The following inclusion criteria have been set for participation in the MoB intervention: (1) clinical diagnosis based on the Diagnostic and Statistical Manual of Mental Disorders-5 for BD; (2) aged between 18 and 65 years; (3) signed the informed consent form; (4) stable mood status at the beginning of the MoB in-person intervention based on clinical assessment, conducted by the principal investigator (AH); (5) experience of the illness for at least 1 year based on the medical record; (6) adequate awareness of the illness, based on the following guide: (a) are you aware of the reason(s) you are using mental health services/under medication? and (b) are you aware of the aim of the educational intervention in which you may participate?; and (7) familiarity with computer use.

The exclusion criteria are: (1) intellectual disability (IQ<70), based on the Wechsler Adult Intelligence Scale [42]; (2) brain damage (eg, following a stroke) based on diagnostic tests; (3) acute phase of the illness, based on clinical assessment and use of the Young Mania Rating Scale (YMRS; total score <12) [43] and/or Beck Depression Inventory (total score <17) [44]; and (4) substance use problems at the beginning of this stage according to the Alcohol Use Disorders Identification Test (AUDIT; total score <9) [45] and Drug Use Disorders Identification Test (DUDIT; total score <2 for women or <6 for men) [46].

All eligible participants will be randomly assigned (in terms of gender, age, duration of illness) into the intervention group and the control (waiting) group. With the aim of obtaining a moderate correlation effect, with 80% statistical power and .05 level of statistical significance, 40 participants are needed in the intervention group and 40 participants are needed in the control (waiting) group.

The criteria for discontinuing participation in the intervention group are disorder relapse and nonadherence to pharmacotherapy (discontinuation of medication).

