#### Effectiveness Evaluation

Evaluation of the effectiveness of the MoB in-person intervention will be based on the degree of improvement in the following outcome variables defined according to the findings of the literature review completed in Stage 1: (1) self-perceived quality of life level, as measured by the World Health Organization Quality of Life Assessment (WHOQOL) tool [47]; (2) self-perceived health-related locus of control, as measured by the Multidimensional Health Locus of Control (MHLC) scale [48]; (3) ability to control impulses, as reflected in one’s sexual and aggressive behavior, measured by the items “aggressive behavior” and “sexual interest” of the YMRS [43]; (4) substance use problems, measured by the AUDIT (alcohol use) [45] and DUDIT (drug use) [46] tools; (5) adherence to pharmacotherapy, measured by the Drug Attitude Inventory (DAI-30) tool [49]; (6) frequency of relapses assessed by the reduction of the number and duration of hospitalizations for the 2 years following the end of the educational intervention; and (7) BD knowledge level assessed by the Bipolar Disorder Knowledge Scale (BDKS) [50].

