The degree of self-perceived quality of life will be measured by the total score in the WHOQOL scale assessment. This is a 1-5 Likert-type scale including 26 items. The minimum score in the scale is 26 and the maximum is 130; higher scores indicate a better outcome. The BD level of knowledge will be measured by the total score in the BDKS. This is a 25-item, true-false scale. The items address diagnosis, etiology, disease course, symptoms, treatment, and life impact BD-related knowledge. The ratio of “true” to “false” responses is assessed; a higher percentage of correct values indicates a better outcome. The degree of ability to control impulses will be measured by the total score in the YMRS. This is a 0-4 Likert scale, including 11 items. The total score of the scale ranges from 0 to 44; a lower total score indicates a better outcome. The degree of adherence to pharmacotherapy will be measured by the total score in the DAI-30. This is a 30-item true-false scale. The ratio of “true” to “false” responses is assessed; a higher percentage of correct values indicates a better outcome. Drug use will be measured by the total score in the DUDIT scale. This is a 1-5 Likert, 11-item scale (total score range: 1-55); a lower total score indicates a better outcome. Alcohol use will be measured by the total score in the AUDIT. This is a 0-4 Likert, 10-item scale (total score range: 0-40); lower scores indicate a better outcome. The degree of self-perceived health-related locus of control will be assessed by the MHLC tool, which is a 6-point Likert (scored from 1 to 6), 18-item scale (Form A). These items are grouped in three subscales corresponding to three different loci of control (ie, internal, others, and fate/luck); higher sum scores in each of the 3 subscales indicate a stronger locus of control. The frequency of relapses will be measured by the number of hospitalizations after completion of the in-person intervention. The number of hospitalizations will be measured as the sum of individual hospitalizations in a high-security psychiatric hospital/setting; the lower the number of hospitalizations, the better the outcome. The duration of relapses will be assessed by the duration of inpatient hospitalizations in days after completion of the in-person intervention. The duration of inpatient hospitalizations will be measured as the sum of the days of hospitalization in a high-security psychiatric hospital/setting; the lower the duration in days of hospitalization, the better the outcome.

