
There will be four evaluation time points. The first evaluation time point will be prior to implementation of the MoB in-person intervention, the second will take place immediately after completion of the MoB in-person intervention, and the third and fourth evaluations will be applied at 6 and 12 months, respectively, after completion of the MoB in-person intervention. These time points have been determined according to the systematic review completed in Stage 1 [14].

The control group will be assessed via the same evaluation tools as the intervention group, and at the same time periods. This will test the null hypothesis that patients who solely receive pharmacotherapy demonstrate the same improvement as the intervention group.

The educational meetings will be held at Cyprus University of Technology in a room specially designed for this purpose that is soundproof, without windows, and chairs placed in a circular arrangement to allow for eye contact, along with small tables on either side to keep notes.

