#### Data Analysis

The means (SD) will be calculated for the scale numeric (sum) scores (YMRS, WHOQOL, MHLC, BDKS, DUDIT, DAI-30, AUDIT, relapse frequency/duration) and frequencies will be calculated for categorical variables (gender, age groups, sex, years in illness groups). Parametric tests (analysis of variance, *t* test) will be applied for comparisons between groups. For all statistical tests, *P* values of .05 or lower will be considered statistically significant. Data will be analyzed through the Statistical Package for Social Sciences (SPSS Inc, version 25.00). To test the relationship between two or more variables, logistic and linear regression analyses will be used. The multiple imputation method will be applied to handle missing data.

### Stage 4

Assessment of the applicability of the MoB digital platform will be based on qualitative (users’ feedback) and quantitative (data analysis) testing. The qualitative assessment will be based on the experience of the users with the platform and on the degree to which they were positively affected by its use. Specifically, the focus of the interviews will be on the impact of the platform on their everyday life, as well as on enhancement of ill health self-management skills according to the participants’ responses to the following open-ended questions: (a) “How would you describe your experience with the use of the MoB digital platform?” (b) “What was the impact of use of the MoB digital platform on your life?” and (c) “What was the impact of the MoB digital platform on your ill health self-management skills?” This process will take place via focus groups discussions. Specifically, two focus groups with 8-12 participants each will be recruited including participants who (a) attended the MoB in-person intervention and had used the platform and (b) solely used the MoB digital platform.

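### Discontinuation for relapse or stopping medication is set for the intervention arm only, and the text does not say that follow-up continues, so the relapse comparison can be biased toward the intervention

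*Protocol article*

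**What the plan says.** All places are in the protocol article, Methods.

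- **Discontinuation rule** (Stage 3, Inclusion and Exclusion Criteria): "The criteria for discontinuing participation in the intervention group are disorder relapse and nonadherence to pharmacotherapy (discontinuation of medication". No corresponding sentence covers the control (waiting) group.
- **Outcomes** (Effectiveness Evaluation): the fifth is "adherence to pharmacotherapy, measured by the Drug Attitude Inventory (DAI-30) tool". The sixth is "frequency of relapses assessed by the reduction of the number and duration of hospitalizations for the 2 years following the end of the educational intervention".
- **Timing** (Effectiveness Evaluation): "The frequency of relapses will be measured by the number of hospitalizations after completion of the in-person intervention". The second evaluation directly follows completion of the sessions, and "the third and fourth evaluations will be applied at 6 and 12 months, respectively, after completion of the MoB in-person intervention".
- **Control arm**: "The control group will be assessed via the same evaluation tools as the intervention group, and at the same time periods" (Effectiveness Evaluation). Under Settings and Sampling the principal investigator "will also make a phone call once or twice per month to reassure their participation in the study".
- **Missing data** (Data Analysis): "The multiple imputation method will be applied to handle missing data".
- **Leaving early** (Intervention Procedure): people who choose to withdraw before the sessions end keep access to the digital platform. Nothing is said there about their later assessments.

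**The concern.** A rule that acts in one arm only, and is triggered by events close to the outcomes, can undo the balance that randomisation created. An intervention participant who relapses or stops medication during the sessions may leave. A control with the same course has no such exit and is actively kept in contact. The participants then compared are all controls against the part of the intervention arm that did well early on.

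The timing wording adds to this. Someone discontinued partway never completes the sessions, so the text does not directly say when that person's evaluations and hospitalisation count begin.

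The events are to be expected. The article's literature review lists relapse among the commonest reasons for quitting such programmes, and its Introduction reports high nonadherence in this population. With 40 per arm, a handful of selective departures could matter. An analysis plan can specify how missing values are treated, but it cannot recover assessments that were never made.

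**Working it through.** **1. Inputs.** From the article: 40 per arm; 12 sessions, one per week, so t = 12/52 = 0.231 years; a 2-year hospitalisation count. The article gives no relapse, hospitalisation or nonadherence rate, and no figure of its own on this point to reproduce. Assumed: a mean event rate λ of 0.3 to 0.8 per person-year, and a gamma-distributed individual rate multiplier (frailty) with mean 1 and variance v of 0.5 to 2. One event type stands for both the trigger and the outcome.

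**2. Model.** There is no treatment effect. Intervention participants with at least one event during the sessions are dropped; all controls are kept. Given no event in time t, the expected multiplier is 1/(1 + vλt). Hence:

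- apparent rate ratio = 1/(1 + vλt), whatever the length of later follow-up;
- share of the arm dropped = 1 − (1 + vλt)^(−1/v).

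**3. Results.**

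| λ | v | vλt | Apparent ratio | Share dropped | Of 40 |
|---|---|---|---|---|---|
| 0.3 | 0.5 | 0.035 | 0.967 | 6.6% | 2.6 |
| 0.5 | 1 | 0.115 | 0.897 | 10.3% | 4.1 |
| 0.8 | 2 | 0.369 | 0.730 | 14.5% | 5.8 |

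With v = 0 the ratio is 1. Any variation in risk between participants takes it below 1, so the direction does not depend on the chosen values.

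**4. Size against noise.** In the middle row over 2 years the control mean is 2 × 0.5 = 1.0 event, with variance 1.0 + 1 × 1.0² = 2.0. The bias is 1.0 × (1 − 0.897) = 0.103 events. The standard error of the difference with 40 per arm is about √(2 × 2.0/40) = 0.316. The bias is about one third of a standard error.

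**5. Check by simulation.** Two-year counts, 40 per arm, t test, 1,000 trials per setting, no true effect, assumed rates up to 1.0 per year, with an assumed 10% to 20% stopping medication in a way linked to the same liability.

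- All randomised participants followed: ratio 0.98 to 1.02, two-sided rejection 3.5% to 5.7%.
- Intervention participants dropped for either trigger during the sessions: ratio 0.55 to 0.93, with a significant result favouring the intervention in 3% to 26% of trials (nominal about 2.5%).

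The second range is wider because it adds the assumed link between nonadherence and relapse risk.

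**6. Imputation.** The calculations drop participants, whereas the plan imputes. A model without relapse or medication status would predict a discontinued participant's later values from people with, on average, a better course. A model that includes both could borrow from controls who relapsed and were still observed. For that, both events must be recorded in both arms during the session period, and the relapse outcome as worded starts only afterwards.

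**The case against.** The strongest reply is that the sentence concerns the sessions and nothing more. It stands in a section that sets criteria for taking part in the intervention, and a waiting-list arm has no sessions to stop, so a one-arm rule is natural. On that reading follow-up continues and there is no bias of this kind. The reading is possible, and a reader should not infer that the protocol says discontinued participants are removed from the trial or the analysis. But it does not say that they are kept either, and its phrase refers to participation.

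Second, the triggers are not the outcome measures. Relapse is broader than admission to a secure psychiatric setting, and stopping medication is not a score on a drug-attitude inventory. This stands: the overlap is by construct, and the one-event model is an illustration only.

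Third, controls never complete the sessions either, yet they are assessed at matching periods, so a calendar clock must exist. This also stands. A reader might infer that the outcome of a discontinued participant cannot be defined. The text does not go that far; the same clock could serve, but it has to be named.

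Fourth, analysis sets and imputation models usually belong in an analysis plan that is not shown. That is fair for the details. It does not cover whether data are collected after discontinuation, which the protocol has to settle.

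**Conclusion.** The concern holds as a correctable weakness in the protocol's wording. An arm-specific rule, triggered by events close to two outcomes, is combined with timing from completion and no statement that follow-up continues. If participants leave follow-up under it, the relapse comparison shifts toward the intervention.

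The direction needs only that relapse risk varies between participants. The size rests on assumptions: for relapse during the 12 weeks, a null rate ratio of about 0.73 to 0.97 if those participants are dropped, under the rates and frailty stated above. If only attendance stops, this bias is nil.

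Three stronger readings are tempting and not supported.

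- Much larger distortions appear if a relapse during follow-up also ends counting in the intervention arm (an apparent ratio of 0.62 in the central case). No text says that the rule runs on after the sessions end.
- Quality of life, knowledge and adherence scores might be thought to be inflated too. Only event rates were calculated.
- It does not follow that the randomised comparison is lost. That would require discontinued participants actually to go unfollowed or be left out of the analysis.

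**What to change.** The clinical rule itself stays with the investigators. The protocol should add that:

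1. meeting these criteria ends session attendance only;
2. all randomised participants of both arms remain in all four evaluations and in the hospitalisation count;
3. evaluations and counts run from a date common to both arms, for example the scheduled end of the 12-week session period, in place of individual completion;
4. the comparison is by randomised arm;
5. relapse and discontinuation of medication are recorded in both arms, including during the session period, and enter the imputation model.

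Counting relapses from randomisation, or adding a sensitivity analysis with unfavourable values for those who left after relapse, is optional and can be left to the analysis plan.

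The cost is a few sentences and continued questionnaires for a few participants: roughly 3 to 6 of 40 under the assumed relapse rates, more if stopping medication is also common.

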#### Intervention Procedure

The form of this intervention will be in groups or in person according to the participant’s choice (similar to the data collection process as detailed above). Additionally, all participants of this group will have access to the MoB digital platform and will be assessed via a checklist on the frequency and extent to which they use the digital platform in each in-person session.

The implementation methodology of the MoB in-person intervention will include videos and PowerPoint presentations, as well as interactive learning methods such as role playing, empowerment exercises, and live discussions.

The MoB in-person intervention will comprise a total of 12 educational sessions. Each session will have a duration of 1.5 hours and the maximum number of participants in the groups will be 12 patients. At the beginning of each session, the participants will be given the opportunity to record their feedback for the previous session and the impact of the training intervention so far for themselves and for their families/significant others. The intervention will be performed at Cyprus University of Technology and will be implemented by the principal investigator (AH). Participation in the educational intervention is free of charge. Moreover, there is no financial benefit for those participating in the study (participants, researchers) in terms of reimbursement or any other material benefit.

Those who wish to withdraw participation prior to completion of the intervention will be able to continue to receive information/knowledge about their illness through the digital platform.

The control (waiting) group will only have access to the MoB digital platform. Yet, it should be noted that the control (waiting) group will also receive the MoB in-person intervention if its effectiveness is shown at the end of the study. In this way, all participants will be given the chance to receive the MoB intervention.

#### Effectiveness Evaluation

Evaluation of the effectiveness of the MoB in-person intervention will be based on the degree of improvement in the following outcome variables defined according to the findings of the literature review completed in Stage 1: (1) self-perceived quality of life level, as measured by the World Health Organization Quality of Life Assessment (WHOQOL) tool [47]; (2) self-perceived health-related locus of control, as measured by the Multidimensional Health Locus of Control (MHLC) scale [48]; (3) ability to control impulses, as reflected in one’s sexual and aggressive behavior, measured by the items “aggressive behavior” and “sexual interest” of the YMRS [43]; (4) substance use problems, measured by the AUDIT (alcohol use) [45] and DUDIT (drug use) [46] tools; (5) adherence to pharmacotherapy, measured by the Drug Attitude Inventory (DAI-30) tool [49]; (6) frequency of relapses assessed by the reduction of the number and duration of hospitalizations for the 2 years following the end of the educational intervention; and (7) BD knowledge level assessed by the Bipolar Disorder Knowledge Scale (BDKS) [50].

The degree of self-perceived quality of life will be measured by the total score in the WHOQOL scale assessment. This is a 1-5 Likert-type scale including 26 items. The minimum score in the scale is 26 and the maximum is 130; higher scores indicate a better outcome. The BD level of knowledge will be measured by the total score in the BDKS. This is a 25-item, true-false scale. The items address diagnosis, etiology, disease course, symptoms, treatment, and life impact BD-related knowledge. The ratio of “true” to “false” responses is assessed; a higher percentage of correct values indicates a better outcome. The degree of ability to control impulses will be measured by the total score in the YMRS. This is a 0-4 Likert scale, including 11 items. The total score of the scale ranges from 0 to 44; a lower total score indicates a better outcome. The degree of adherence to pharmacotherapy will be measured by the total score in the DAI-30. This is a 30-item true-false scale. The ratio of “true” to “false” responses is assessed; a higher percentage of correct values indicates a better outcome. Drug use will be measured by the total score in the DUDIT scale. This is a 1-5 Likert, 11-item scale (total score range: 1-55); a lower total score indicates a better outcome. Alcohol use will be measured by the total score in the AUDIT. This is a 0-4 Likert, 10-item scale (total score range: 0-40); lower scores indicate a better outcome. The degree of self-perceived health-related locus of control will be assessed by the MHLC tool, which is a 6-point Likert (scored from 1 to 6), 18-item scale (Form A). These items are grouped in three subscales corresponding to three different loci of control (ie, internal, others, and fate/luck); higher sum scores in each of the 3 subscales indicate a stronger locus of control. The frequency of relapses will be measured by the number of hospitalizations after completion of the in-person intervention. The number of hospitalizations will be measured as the sum of individual hospitalizations in a high-security psychiatric hospital/setting; the lower the number of hospitalizations, the better the outcome. The duration of relapses will be assessed by the duration of inpatient hospitalizations in days after completion of the in-person intervention. The duration of inpatient hospitalizations will be measured as the sum of the days of hospitalization in a high-security psychiatric hospital/setting; the lower the duration in days of hospitalization, the better the outcome.

There will be four evaluation time points. The first evaluation time point will be prior to implementation of the MoB in-person intervention, the second will take place immediately after completion of the MoB in-person intervention, and the third and fourth evaluations will be applied at 6 and 12 months, respectively, after completion of the MoB in-person intervention. These time points have been determined according to the systematic review completed in Stage 1 [14].

The control group will be assessed via the same evaluation tools as the intervention group, and at the same time periods. This will test the null hypothesis that patients who solely receive pharmacotherapy demonstrate the same improvement as the intervention group.

The educational meetings will be held at Cyprus University of Technology in a room specially designed for this purpose that is soundproof, without windows, and chairs placed in a circular arrangement to allow for eye contact, along with small tables on either side to keep notes.

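### Impulse control is defined as two YMRS items in one place and as the 11-item YMRS total in another, and the BDKS and DAI-30 descriptions include a ratio that does not measure correctness

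*Protocol article*

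**What the plan says.** All the passages are in Methods, Stage 3, of the protocol article.

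- **Effectiveness Evaluation, numbered outcome list, item 3.** Impulse control is the ability reflected in sexual and aggressive behavior, "measured by the items “aggressive behavior” and “sexual interest” of the YMRS".
- **Effectiveness Evaluation, description of the instruments.** "The degree of ability to control impulses will be measured by the total score in the YMRS". The text continues: "This is a 0-4 Likert scale, including 11 items", and "The total score of the scale ranges from 0 to 44; a lower total score indicates a better outcome".
- **Inclusion and Exclusion Criteria.** The criterion on acute illness rests on clinical assessment and "use of the Young Mania Rating Scale (YMRS; total score <12"), with or without a depression inventory.
- **Data Analysis.** Means and SDs are planned for the "scale numeric (sum) scores (YMRS, WHOQOL, MHLC, BDKS, DUDIT, DAI-30, AUDIT, relapse frequency/duration"). No two-item YMRS score is named, and neither is the 11-item total.

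For the BDKS (25 true-false items) and the DAI-30 (30 true-false items), the instrument description first says that each is measured by its total score. It then says for each that the ratio of 'true' to 'false' "responses is assessed; a higher percentage of correct values indicates a better outcome".

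**The concern.** The two definitions of impulse control are different variables, and nothing in the article reconciles them. One is confined to the behavior that the outcome list names. The other is the whole scale, which the article itself uses elsewhere to detect acute illness. A group difference on the total could therefore reflect general mood state and still be reported as better impulse control.

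The outcome is not incidental. The Introduction and the Aim both list impulse control among the effectiveness targets, and the review in Stage 1 found that none of the included studies had assessed it. The text shown names no primary outcome. With two definitions both admissible under the protocol, the choice could be made after the data are seen.

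The secondary concern is the ratio clause. On a true-false scale, the ratio of 'true' to 'false' responses counts how often a person marks 'true', not how often the person is right. Knowledge is the first effectiveness aim, and the BDKS is also an outcome in Stage 4, so its scoring rule should be unambiguous.

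**Working it through.** **1. Impulse control**

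Inputs: 11 items, each scored 0-4, and a stated total range of 0-44 (Effectiveness Evaluation); two named items (outcome list).

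- Total score: 11 × 0 = 0 to 11 × 4 = 44. The stated range is reproduced.
- Two-item sum under the same scoring: 2 × 0 = 0 to 2 × 4 = 8.
- Share of the total's range carried by the two items: 8/44 = 18%.

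The remaining 36 of 44 points come from items that the outcome list does not tie to impulse control. The wording in Data Analysis fits a sum of two items as well as a sum of eleven, so it does not decide the matter.

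**2. BDKS and DAI-30 ratio, read literally**

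Inputs: N = 25 items (BDKS) and N = 30 items (DAI-30), from Effectiveness Evaluation. The article gives no answer key, so the number keyed true, k, is an assumption and is varied.

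If each item is answered correctly with probability p, the expected number of 'true' responses is k·p + (N − k)(1 − p). The expected number of 'false' responses is N minus that. At p = 0.5 both equal N/2, so the ratio of expected counts is 1.00 for any key. At p = 1 the ratio is k/(N − k).

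| Scale | k (assumed) | 50% correct | 100% correct | Direction as correctness rises |
|---|---|---|---|---|
| BDKS | 8 | 1.00 | 8/17 = 0.47 | falls |
| BDKS | 13 | 1.00 | 13/12 = 1.08 | nearly flat |
| BDKS | 16 | 1.00 | 16/9 = 1.78 | rises |
| DAI-30 | 10 | 1.00 | 10/20 = 0.50 | falls |
| DAI-30 | 15 | 1.00 | 15/15 = 1.00 | flat |
| DAI-30 | 20 | 1.00 | 20/10 = 2.00 | rises |

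Averaging each BDKS respondent's own ratio, with all-'true' respondents left out, gives about 1.09 at 50% correct instead of 1.00. The pattern across keys is the same.

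Two further checks on the BDKS:

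- A respondent who marks 'true' throughout has a ratio of 25/0, which is undefined. The share correct is 8/25 = 32%, 13/25 = 52% or 16/25 = 64% for k = 8, 13 or 16.
- With k = 12, anyone giving 12 'true' responses has a ratio of 12/13 = 0.92. If all 12 fall on false-keyed items, only 1 of 25 answers is right (4%). If all 12 fall on true-keyed items, 25 of 25 are right (100%).

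**The case against.** **On impulse control**, one could say that a statistical analysis plan will settle the score. That does not answer the point. The article leaves nothing out here: it states two definitions, and a later plan would have to overrule one of them. Two limits on the criticism do stand. A reader might infer that the analysis is committed to the 11-item total, but Data Analysis says only YMRS and sum, which a two-item sum also satisfies. A reader might also infer that the other nine items have nothing to do with impulse control. The article does not list those items, so this cannot be checked from it. What can be said is that the outcome list ties only two items to the construct.

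**On the BDKS and DAI-30**, the case against is stronger. A reader might infer that the two scales are scored by the ratio alone and that the knowledge aim could therefore read as no effect. The documents do not support that. The same description gives a total score and takes a higher percentage correct as better, and Data Analysis lists both scales as sum scores. A percentage correct and a sum of correct answers are one measure on two scales when all items are answered, so those two rules do not conflict. The near-flat result also holds only near a balanced key.

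The clause may also have been meant as right to wrong answers. That ratio does rise with correctness: 15 of 25 gives 15/10 = 1.5, and 20 of 25 gives 20/5 = 4.0. Even so, it is undefined at a perfect score and is a different variable from the sum score. The text, moreover, speaks of responses on a true-false scale. The clause still needs correcting, but as one faulty clause beside workable rules.

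**Conclusion.** The impulse-control contradiction is wrong as written and rests on no assumption beyond the article's own item scoring: 0-8 against 0-44 for the same outcome, with the larger score also serving as the screen for acute illness. It should be resolved before analysis. Impulse control is one of seven listed outcomes, so the error affects that outcome and not the whole evaluation.

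The ratio clause for the BDKS and DAI-30 is a secondary wording error. Read literally it does not measure correctness, and its direction depends on the key. The size of the distortion cannot be stated, because the key is not given. Under assumed BDKS keys of 8 to 16 true items, the ratio at full correctness ranges from 0.47 to 1.78.

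**What to change.** - **Impulse control.** State one definition and use it in the outcome list, the instrument description and Data Analysis. The two-item sum is preferable, because those are the items that the outcome list ties to the construct. Report the YMRS total separately, labelled as mood state. If the sponsor prefers the total, the outcome list should say so and the outcome should be named for what the total measures.
- **BDKS.** Delete the ratio clause. Score the number or percentage of the 25 items answered correctly.
- **DAI-30.** Delete the ratio clause. Score the number or percentage of the 30 items answered in the keyed direction, since the article does not define a correct answer for an attitude inventory.

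Both scores then agree with the sum scores in Data Analysis. The cost is wording only: the questionnaires, visits and data collected stay the same. The change should be dated and made before outcome data are examined.
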